**Results:**

In this study, two comparative cohorts and an observational cohort will be set up. The primary outcome is the effect of emergency surgery, which is subject to assessment using the total mortality and comparison in the survival rate of SSICH patients on LOAPT between surgical treatment and conservative treatment. The second outcome is the safety of surgery, with the postoperative hemorrhagic complication which is compared between the operated SSICH patients on and not on LOAPT. Based on the observation of the characteristics and outcome of SSICH patients on LOAPT, the ischemic events after discontinuing LOAPT will be further addressed, and the coagulation function assessment system for operated SSICH patients on LOAPT will be established.

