## Results

China National Clinical Research Center for Neurological Diseases will be responsible for data analysis. Sample size was calculated by using PASS (Version 15, NCSS corporation, American). All sample size calculations were performed by conducting two-sided test, *α* = 0.05 and *β* = 80% (the degree of control = 80%). In this study, two comparison groups will be established, with the primary and secondary outcomes as the focus in this study. According to our unpublished data collected from 7 participating centers in 2019, for SSICH patients on LOAPT, the total mortality was about 30% for operated patients and 45% for the patients receiving conservative treatment, with the ratio of two groups reaching about 1:1.5. Moreover, for operated SSICH patients, the incidence of PIB was about 23% for patients on LOAPT and 10% for patient not on LOAPT, with the ratio of two groups reaching about 1:2.5. With regard to the primary outcome, our sample size was calculated as 196 (196 SSICH patients on LOAPT, operation group: *n* = 78; conservation group: *n* = 118). As for the secondary outcome, the sample size was 247 (247 operated SSICH patients, LOAPT group: *n* = 70; non-LOAPT group: *n* = 177). Moreover, in order to establish the coagulation function assessment system, the area under curve was expected to be 0.7, and the sample size was set to 92 (92 operated SSICH patients on LOAPT, PIB group: *n* = 23; non-PIB group: *n* = 69). In this case, a minimum of 387 SSICH patients (includes 118 patients on LOAPT receiving conservative treatment, 92 patients on LOAPT receiving emergency surgery, and 177 patients not on LOAPT receiving emergency surgery) may be required in this study to reach our research objective. Thus, to ensure final statistics, a total of 400 patients (patients on LOAPT receiving conservative treatment, *n* = 120; patients on LOAPT receiving emergency surgery, *n* = 100; patients not on LOAPT receiving emergency surgery, *n* = 180; Fig. 1) will be recruited. In this study, 10% of patients would be lost during follow-up. Finally, we decided to recruit 450 appropriate patients.

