All statistical analyses were conducted with the assistance of SPSS (Version 22.0, IBM, American). The data was indicated as mean (x) ± standard deviation (SD) for normally distributed data, median, and interquartile range (IQR) for skewed distributed data or number (*n*) and percentage (%). In this study, two main comparative groups and an observational cohort will be established, as shown in Fig. 1. Firstly, in order to investigate the effect of emergency neurosurgery, a comparison will be performed between SSICH patients on LOAPT receiving conservative treatment and those receiving emergency neurosurgery. Secondly, in order to investigate the safety of emergency neurosurgery, a comparison will be performed between operated SSICH patients on LOAPT and those not on LOAPT. Thirdly, in order to investigate the intra/postoperative complications and the risk of ischemic disease after discontinuing antiplatelet treatment, the characteristics of SSICH patients on LOAPT will be analyzed; moreover, because the history of previous neural ischemic events or cardiac events could affect the risk of postoperative ischemic events, we would perform the subgroup analysis depending on this history to further investigate the effect of discontinuing antiplatelet treatment on the risk of ischemic disease. The difference will be compared by conducting χ^2^ test, Mann-Whitney *U* tests, or Student’s *t* tests. The independent risk factors were analyzed by logistic regression, while the factors with *p* < 0.10 in univariate analysis were entered into a multivariate logistic regression model. The result was indicated as odd ratio (OR) and 95% confident interval (CI). The receiver operating characteristic (ROC) curve analysis was performed to test the prediction value of different parameters and different methods. An area under the curve (AUC) in a ROC analysis of ≥ 0.7 is considered as a clinical utility, while *p* value of < 0.05 was treated as statistically significant.

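### The safety comparison of PIB rests on a p < 0.05 difference test, and no estimate with a confidence interval for LOAPT is assured when that test is non-significant

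*Protocol article*

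**What the plan says.** The abstract ties safety to one comparison: "The second outcome is the safety of surgery, with the postoperative hemorrhagic complication which is compared between the operated SSICH patients on and not on" (the sentence goes on to name LOAPT). The statistical paragraph of the Results section repeats it: "in order to investigate the safety of emergency neurosurgery, a comparison will be performed between operated SSICH patients on LOAPT and those not on LOAPT". Among postoperative hemorrhagic complications, the outcomes section makes PIB the main focus.

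The method is given in general terms: "The difference will be compared by conducting χ^2^ test, Mann-Whitney *U* tests, or Student’s *t* tests". For a binary endpoint such as PIB that means χ². The threshold is "while *p* value of < 0.05 was treated as statistically significant".

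The same paragraph plans logistic regression for independent risk factors. Only factors with univariate p below 0.10 go forward to the multivariable model, and the odds ratio with 95% CI is mentioned directly after that. The paragraph does not say that LOAPT status stays in a PIB model regardless of its p-value.

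The sample size paragraph sizes the comparison to detect harm. "All sample size calculations were performed by conducting two-sided test", and the planning rates are these: "the incidence of PIB was about 23% for patients on LOAPT and 10% for patient not on LOAPT", a difference of 13 points.

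**The concern.** A difference test can show that operated patients on LOAPT bleed more. It cannot show that they do not bleed importantly more, because a non-significant result may come from a small excess or from too little information. The interval separates the two, and the plan does not secure it. Entry to the multivariable model depends on the univariate p-value, so LOAPT can be left out exactly when the comparison is non-significant.

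The article could then report only two percentages and a p-value above 0.05 for its safety question. It says in the Background that intraoperative and postoperative bleeding can be fatal, and it intends the results to inform management. A bare non-significant p-value could reassure a reader while the data still allow the excess on which the study was planned.

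**Working it through.** **Inputs.** From the sample size paragraph: PIB 23% on LOAPT and 10% not on LOAPT, two-sided 0.05, 80% power, and 100 operated LOAPT and 180 operated non-LOAPT patients before the allowance for loss to follow-up. The true LOAPT rates of 20% and 18% are assumptions, chosen to show what happens if the 2019 estimate is somewhat high.

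**1. The plan's own size.** The article states "with the ratio of two groups reaching about 1:2.5" and "the sample size was 247 (247 operated SSICH patients, LOAPT group: *n* = 70; non-LOAPT group: *n* = 177"). The usual pooled formula, with k = 2.5 and p̄ = (0.23 + 2.5 × 0.10)/3.5 = 0.1371, gives

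n₁ = [1.96√(p̄(1−p̄)(1+1/k)) + 0.8416√(0.23×0.77 + 0.10×0.90/k)]² / 0.13² = (0.798 + 0.389)² / 0.0169 ≈ 83.3.

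That is 84 + 210 = 294, so 247 does not reproduce; 70 vs 177 has about 74% power. The planned 100 vs 180 has about 82%. The steps below use 100 vs 180, so they do not depend on this discrepancy.

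**2. Chance of a non-significant result.** Exact enumeration of two independent binomials, uncorrected χ², |z| ≤ 1.96, 100 vs 180, control 10%. The last column applies the same enumeration with |z| ≤ 1.645, meaning that LOAPT fails the entry rule for the multivariable model.

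| True LOAPT PIB | Non-significant at 0.05 | Univariate p ≥ 0.10 |
|---|---|---|
| 23% (plan) | 17% | 11% |
| 20% (assumed) | 36% | 25% |
| 18% (assumed) | 52% | 40% |

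Normal-approximation check at 20% vs 10%: p̄ = (20 + 18)/280 = 0.1357, null SE = 0.0427, alternative SE = √(0.16/100 + 0.09/180) = 0.0458. Power = Φ((0.10 − 1.96 × 0.0427)/0.0458) ≈ 64%, so 36% are non-significant. With a continuity correction the figures are higher: 22% at 23% and 43% at 20%.

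**3. What a non-significant result can look like.** Take 18/100 vs 18/180.
- Pooled rate 36/280 = 0.1286, SE = √(0.1286 × 0.8714 × (1/100 + 1/180)) = 0.0417, z = 0.08/0.0417 = 1.92, p = 0.055.
- Wilson limits: 11.7% to 26.7% (LOAPT) and 6.4% to 15.3% (non-LOAPT).
- Newcombe lower limit: 0.08 − √((0.18 − 0.117)² + (0.153 − 0.10)²) = −0.002.
- Newcombe upper limit: 0.08 + √((0.267 − 0.18)² + (0.10 − 0.064)²) = 0.174.

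The interval of −0.2 to 17.4 points contains both 0 and 13. On the odds scale the result is 1.98 (0.98 to 4.00). The plan's own rates correspond to (0.23/0.77)/(0.10/0.90) = 2.69, which is inside.

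**4. Where the interval can be lost.** In step 3, p = 0.055 is below 0.10, so LOAPT would still enter the model if it were a candidate. With 16/100 vs 18/180, z = 1.47 and p = 0.14, so it would not. The Newcombe interval is then 0.06 − √((0.16 − 0.101)² + (0.153 − 0.10)²) = −1.9 points to 0.06 + √((0.244 − 0.16)² + (0.10 − 0.064)²) = 15.1 points. It again contains 0 and 13, but the entry rule would keep LOAPT, and so its odds ratio, out of the multivariable model.

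**The case against.** The strongest reply is that the article makes no error of inference. It nowhere says that p above 0.05 will be read as safe, and its aims are worded as investigating and evaluating. It expects more bleeding on LOAPT, and a two-sided test sized on that expectation is coherent, with about 82% power at the planned numbers. It also plans percentages and an odds ratio with 95% CI. PIB is not the only basis for judging surgery, since mortality under surgery versus conservative treatment is the primary outcome. Details of interval methods and interpretation often sit in an analysis plan that is not shown.

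Most of this stands. A reader might infer that the plan treats a non-significant test as its route to declaring surgery safe. The documents do not support that, because they state no rule for declaring safety at all. A reader might also infer that a non-inferiority margin is missing and must be imposed. The documents support no margin, and a strict one would be a real trade-off: with 10% PIB in both groups, the upper limit falls below 5 points in only 22% of studies of this size.

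What does not stand is that the planned odds ratio answers the point. The article itself fixes the p < 0.10 entry rule, and that rule works against having an estimate for LOAPT when one is most needed.

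**Conclusion.** The point holds in a limited form. The safety comparison is analysed by a difference test, and the interval needed to read a non-significant result is not assured. The test is suitable for detecting an excess; it is insufficient for a favourable conclusion.

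The size depends on the true LOAPT rate, which is unknown. Only the 17% rests on the plan's own figures; the 36% and 52% rest on assumed rates. All assume 10% control PIB, 100 vs 180 evaluable patients and an uncorrected χ². No claim is made that the investigators intend to equate non-significance with safety, or that the design must become a non-inferiority comparison. This is a low-cost improvement to the analysis text.

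**What to change.** In the statistical paragraph of the Results section:

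1. Make the PIB risk difference (LOAPT minus non-LOAPT, operated patients) with its two-sided 95% CI the reported safety result, whatever the p-value.
2. Keep LOAPT status in the PIB logistic model regardless of its univariate p-value, so that an adjusted odds ratio with CI is always available.
3. State that a non-significant test will not be read as evidence of safety, and that a result whose CI includes both 0 and the plan's 13-point excess will be reported as inconclusive.

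The 13 points serve only as the plan's own reference for what the data have failed to rule out. They are not an acceptable excess, and no formal margin is required.

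The cost is a few sentences and a little more reporting, with no extra patients or data. Some results that would have read as no significant difference will be labelled inconclusive; with true rates of 20% vs 10%, about 27% of studies would carry that label.

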### Qualification of participating center

To avoid participant bias while ensuring the sufficient number of cases included to reach our conclusion, all patients were recruited at the same time, and 7 neurosurgical centers were carefully selected considering the following criteria. Firstly, each center covers at least two communities or works as referral units for hemorrhagic stroke. Secondly, the center can carry out various treatment for SSICH, including all varieties of surgery and conservative treatment. Thirdly, the center is capable to admit more than 100 SSICH patients annually. According to an incomplete data, a total of 500 SSICH patients were evaluated across the 7 centers in 2019. Meanwhile, each center can fully represent the level of diagnosis and treatment of SSICH at a national level. Therefore, the centers involved in this study are considered representative.

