### Ethics and public involvement

Patients or the public were not directly involved in design or conduct of the study. This study was granted approval from Institutional Review Board of Beijing Tiantan Hospital, and the research would be conducted in strict accordance with the declaration of Helsinki and Human Biomedical Research Ethical Issues. In this study, researchers are not able to use randomized controlled trials; thus, all recruited SSICH patients will not be affected by normal course of diagnosis and treatment. When SSICH patients are included, they will be followed up until 6 months after the occurrence of primary hemorrhage.

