The last focus of this study is ischemic complication after discontinuing antiplatelet medication. It is worth mentioning that the patients on antiplatelet medication are put at high risk of developing ischemic diseases including cardiovascular diseases and ischemic stroke. After a long period of discontinuing antiplatelet treatment, just for surgery, it is possible for these patients to develop ischemic diseases perioperatively or postoperatively [27]. This risk may be significantly higher for patients with ischemic stroke as neurosurgery could affect the cerebral blood flow and perfusion [2]. After the treatment of spontaneous intracranial hemorrhage, it is advisable to resume antiplatelet treatment. However, what confuses neurosurgeons is when and how to safely re-start antiplatelet medication. Moreover, there is currently still no relevant study reporting the incidence and risk factors of ACCE after neurosurgery in SSICH patients on LOAPT. Thus, credible evidence is needed to guide postoperative management. In this study, the patients will be followed up until 6 months after primary hemorrhage to investigate the risk of ACCE and the association between the discontinuation of antiplatelet treatment and ischemic complications. It is believed that this study will also provide an evidence to prevent SSICH patients on LOAPT from the development of ischemic complications and a basis for further investigation into the safe resumption of antiplatelet treatment in the future.

Based on our current study design, however, there remain some questions left unresolved. The first one is the indications of neurosurgery for SSICH patients on LOAPT. The second one is the effect of craniotomy, endoscopy, and minimally invasive surgery on SSICH patients on LOAPT. The third one is the advantage of different tools in assessing platelet function. The fourth one is when and how to resume antiplatelet treatment after neurosurgery. Surgical outcome and safety tend to be what neurosurgeons focus on. Despite the limitations to which our current study is subject, it is still believed that our study could provide a basis for the further exploration of appropriate treatment strategy for spontaneous intracranial hemorrhage patients on LOAPT.

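### The PIB safety contrast pools 7 centres and all operation types, and the planned model guarantees a place to none of centre, procedure or LOAPT, so differences in mix could bias it in either direction

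*Protocol article*

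**What the plan says.** The Results section of the protocol article fixes the safety contrast: "a comparison will be performed between operated SSICH patients on LOAPT and those not on LOAPT". Differences are tested by χ², Mann-Whitney or t test, so a yes/no outcome such as PIB gets the χ². The same section plans a logistic regression for independent risk factors, in which a factor joins the multivariable model only if its univariate p value is below 0.10. The one subgroup analysis named there is by ischaemic or cardiac history, for ischaemic risk.

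Other sections describe what is being pooled. Under Qualification of participating center, each of the 7 sites is chosen partly because "the center can carry out various treatment for SSICH, including all varieties of surgery and conservative treatment". Under Ethics and public involvement, treatment is not randomised and "all recruited SSICH patients will not be affected by normal course of diagnosis and treatment". The Discussion lists among the questions this design leaves open "the effect of craniotomy, endoscopy, and minimally invasive surgery on SSICH patients on LOAPT". The section on thrombelastography reserves platelet-function testing for patients on LOAPT, so clinicians know LOAPT status. The Data collection section puts intraoperative findings on the case report form.

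**The concern.** Both groups in this contrast are operated, so the choice between surgery and conservative care is not the issue. The issue is where and how the operation is done. If patients on LOAPT are concentrated in centres with lower or higher bleeding rates, or if their mix of craniotomy, endoscopic and minimally invasive operations differs, the pooled PIB difference combines the LOAPT effect with the centre or procedure effect.

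The logistic model could remove some of this, but its entry rule does not ensure that it will. It lets univariate p values decide whether centre, procedure and even the exposure of interest are in the model. When two factors pull against each other, univariate screening is at its weakest, because each hides the other.

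The stake is how the secondary outcome is read. A similar PIB rate could mean that LOAPT adds little bleeding, or that the groups differed in centre or technique. A large difference has the same ambiguity. The pooled contrast alone cannot separate these readings.

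**Working it through.** **Inputs from the Results section.** PIB rates: "the incidence of PIB was about 23% for patients on LOAPT and 10% for patient not on LOAPT". Allocation of operated patients, LOAPT to non-LOAPT: 1 to 2.5. Error rates: "two-sided test, *α* = 0.05 and *β* = 80" (in per cent, evidently the power). Stated size: "As for the secondary outcome, the sample size was 247" (70 on LOAPT, 177 not). The planned operated groups are 100 and 180.

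**The plan's own figure.** With p1 = 0.23, p2 = 0.10, k = 2.5 and p̄ = (0.23 + 2.5 × 0.10)/3.5 = 0.137, the pooled-variance formula is

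n1 = [1.96√(p̄(1 − p̄)(1 + 1/k)) + 0.84√(p1(1 − p1) + p2(1 − p2)/k)]² / (p1 − p2)².

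This gives 84 + 210 = 294, not 247. The unpooled version gives 99 + 247 = 346, so the stated total equals the larger arm of that calculation. This is a separate matter. What counts here is power at the planned sizes:

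- Pooled rate: (23 + 18)/280 = 0.146.
- Standard error under the null: √(0.146 × 0.854 × (1/100 + 1/180)) = 0.0441.
- Standard error under the alternative: √(0.1771/100 + 0.09/180) = 0.0477.
- Power: Φ((0.13 − 1.96 × 0.0441)/0.0477) = 82%. At 70 and 177 it is 74%.

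**How far the mix could move the contrast (illustration only).** Assume non-LOAPT PIB of 15% after craniotomy and 5% after minimally invasive surgery in a 50:50 mix (10% overall), and that LOAPT multiplies each by 2.3. None of these procedure risks or mixes is in the documents. With craniotomy share f among LOAPT patients, their pooled PIB is 2.3 × (0.15f + 0.05(1 − f)):

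| f | LOAPT PIB | Pooled risk ratio |
|---|---|---|
| 20% | 16.1% | 1.6 |
| 35% | 19.6% | 2.0 |
| 50% | 23.0% | 2.3 |
| 65% | 26.5% | 2.65 |
| 80% | 29.9% | 2.99 |

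The within-procedure risk ratio is 2.3 in every row. In the rows for 50%, 35% and 20%, χ² power at 100 vs 180 is 82%, 61% and 33%.

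**What the p < 0.10 screen does (simulation, 40,000 runs, 100 vs 180).**

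- At f = 20% above, LOAPT passes the screen in about 44% of runs. Stratifying by procedure returns a median Mantel-Haenszel risk ratio of 2.3, with 70% power.
- In a second scenario, less invasive surgery halves PIB, its share is 70% in LOAPT and 30% in non-LOAPT patients, and the LOAPT odds ratio is 2.69 within each procedure. Procedure passes in about 25% of runs and LOAPT in about 60%. The crude odds ratio is 1.97 with 48% power; stratified by procedure it is about 2.7 with 70% power.
- With equal mix (30% in both groups) the crude odds ratio is 2.66, so there is almost no distortion.

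**Cost of stratifying.** Expected events are 100 × 0.23 + 180 × 0.10 = 41. A fixed-effects model with LOAPT, 2 procedure terms and 6 centre terms has 41/9 = 4.6 events per parameter, which is thin. Mantel-Haenszel needs no such parameters. With no imbalance between groups, simulated power is about 82% unstratified, 82% with 7 centre strata and 80% with 21 centre-by-procedure strata.

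**The case against.** **Technique choice is not documented.** A reader might infer that surgeons who know LOAPT status choose gentler operations for these patients, and that the pooled contrast will therefore hide their excess bleeding. The documents do not support this. No section says who chooses the technique, that LOAPT status influences it, or that the mix differs. The opposite mix would exaggerate the excess. This stands.

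**The 2019 rates already reflect usual practice.** The 23% and 10% come from the participating centres, and the study leaves usual care as it is. Any habitual difference in technique is already in the 23%, and 82% is then already the power of the crude contrast. A fall to 61% or 33% would need practice to change after 2019, which nothing in the article suggests. This also stands: those power figures are illustration, not forecast. The 2019 rates are pooled as well, however, so they do not settle the risk at equal centre or technique.

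**Adjustment is planned.** It is, and centre or procedure may enter the model. But the screen guarantees neither of them, nor LOAPT.

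**Technique may be a mediator.** If technique is chosen because of LOAPT status, it lies on the path to PIB, and conditioning on it answers a different question from the risk under usual practice. This stands for procedure and argues against replacing the pooled contrast. It does not apply to centre.

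**A condensed article leaves covariate lists to other documents.** That is fair for procedure coding and centre handling, whose absence is no fault. But the article does state its contrast, its test and its entry rule, and the entry rule is the weak point.

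**Conclusion.** The point holds in limited form. The stated safety contrast is unadjusted and pooled over centres and operation types, and the only planned adjustment leaves centre, procedure and LOAPT to a univariate screen. It is therefore open to bias in either direction. The size is unknown, because it depends on procedure-specific PIB risks and on the mix by group and centre, neither of which the article reports. Under the assumed risks the pooled risk ratio runs from 1.6 to 3.0 around a constant 2.3; with equal mix there is almost no distortion. The documents do not show that an imbalance exists, and masking of a real excess is a possibility only. The pooled result remains a valid description of PIB under usual practice. This is a cheap improvement, not a flaw that defeats the study.

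**What to change.** - Keep the pooled PIB rates and the χ² test, labelled as the description of risk under usual practice.
- Pre-specify a LOAPT vs non-LOAPT PIB estimate stratified by centre. Use Mantel-Haenszel, or a logistic model that retains LOAPT and centre whatever their p values. With about 41 events, merge sparse centres or use a random centre effect.
- Beside it, report an estimate also stratified by procedure type (craniotomy, endoscopic, minimally invasive), labelled as the effect at equal technique because technique may lie on the causal path.
- Tabulate procedure mix by LOAPT group and centre.
- State that a conclusion that surgery on LOAPT is safe will not rest on the pooled contrast alone if these estimates differ.

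The cost is a few sentences in the analysis section, fixed codes for procedure type on the existing case report form, and a small loss of precision (about 2 points of power with 21 strata when there is no imbalance). Readers will also have more than one estimate to interpret, so each needs its question stated.

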### Study definition

After admission, all of the patients would receive standardized care according to the guidelines. Severe spontaneous intracerebral hemorrhage (SSICH) is confirmed by both severe intracerebral hemorrhage radiologically and clinical coma (GCS < 13).

In definition, “on long-term oral antiplatelet therapy (on LOAPT)” refers to patients that received oral antiplatelet treatment on a continued basis for more than 7 days and discontinued antiplatelet medication no more than 7 days after the occurrence of hemorrhage. Antiplatelet therapy involved aspirin, clopidogrel, and dual antiplatelet treatment. Postoperative intracerebral bleeding (PIB) was defined as rehemorrhage within the operative region or new intracerebral hemorrhage associated with the operation on radiological examination.

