### Data collection

In case the patients meet our criteria, all information, including the demography, clinical information, preoperative radiological data, intraoperative findings, and laboratory and TEG data, will be recorded on the case report form (CRF). After being discharged, all the patients were followed up on a regular basis by outpatient visit and on telephone 3 months and 6 months after primary hemorrhage, respectively. During each follow-up visit, the survival condition, mRS, ACCE, and medication will be recorded. If the patients feel unable to undergo radiological examination in the participating center, a follow-up cranial image will be required. Once radiological examination is completed, the patients’ imaging data will be transmitted to the Tiantan hospital (this center will work as an imaging interpretation center) to reconfirm several events, including SSICH, PIB, and postoperative ischemic disease. During the study, the researchers are required to protect privacy for the patients and ensure the confidentiality of their medical information. The information collection schedule is presented in Table 4.

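### The subgroup split by prior ischaemic history cannot show an effect of discontinuing antiplatelets, because the article defines no comparison by discontinuation

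*Protocol article*

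**What the plan says.** The third aim concerns ischaemic events after antiplatelets are stopped. In Study design it is purely descriptive: the risk of postoperative ischaemic disease in LOAPT patients.

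The statistical paragraph of Results goes further. For this aim "the characteristics of SSICH patients on LOAPT will be analyzed". Because earlier neural ischaemic or cardiac events could affect the risk, "we would perform the subgroup analysis depending on this history", and the stated purpose is "to further investigate the effect of discontinuing antiplatelet treatment on the risk of ischemic disease". The Discussion says follow-up to 6 months will serve to investigate "the association between the discontinuation of antiplatelet treatment and ischemic complications".

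Study definition describes being on LOAPT as continuous use for more than 7 days, together with having "discontinued antiplatelet medication no more than 7 days after the occurrence of hemorrhage". Data collection says that at the 3- and 6-month contacts "the survival condition, mRS, ACCE, and medication will be recorded". The Discussion lists the timing and manner of resuming treatment among the questions the design leaves open.

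For methods, the sentence that begins "The difference will be compared by conducting" names chi-square, Mann-Whitney and t tests. It is followed by "The independent risk factors were analyzed by logistic regression". No method named for this aim uses the time at which treatment stops or restarts.

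**The concern.** An effect of discontinuation is a contrast between patients, or periods of follow-up, that differ in whether the drug is being taken. The only split described for this aim is by history, and the article itself gives the reason for it: history may change the ischaemic risk. A difference between the two history groups would be expected whether or not stopping the drug does anything.

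At stake is the interpretation of the third aim. The Discussion wants this evidence to inform postoperative management and later work on resumption. A higher event rate in patients with prior ischaemic disease, presented under the label the article gives it, would be read as harm from stopping.

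**Working it through.** The article gives no event rate, sample size or power for this aim, so there is no figure of its own to reproduce. The check is mainly one of logic.

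**1. Is there a comparison by discontinuation?**

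| Element | Where | Content |
|---|---|---|
| Population | Results | LOAPT patients only (planned 120 conservative + 100 operated = 220) |
| Exposure | Study definition | Read literally, discontinuation is part of being on LOAPT |
| Split | Results | Prior ischaemic or cardiac history |
| Continuing or restarted comparator | – | None defined |

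Operated patients not on LOAPT cannot serve as comparator, since they had no treatment to stop. The history split yields risk(history) minus risk(no history) among LOAPT patients. That is a prognostic difference. History could show whether a discontinuation effect varies between subgroups, but only if that effect were estimated within each subgroup first.

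**2. How much does death matter?** Results gives total mortality of about 30% with surgery and 45% with conservative treatment. At the planned sizes: 0.30 × 100 + 0.45 × 120 = 30 + 54 = 84 deaths, and 84/220 = 38%. These deaths preclude later ischaemic events and later restart.

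**3. Could the methods named support an off-versus-restarted comparison, if one were attempted?** The article does not plan this. The check only shows why such a claim would need dated exposure.

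Assumptions not in the article: 10% ischaemic risk over 180 days, half of patients due to restart at day 60, constant and independent hazards, and no effect of restarting. Mortality is set at 30%.

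- Event hazard a = −ln(0.9)/180 = 0.000585 per day; death hazard b = −ln(0.7)/180 = 0.001982 per day.
- Probability of an event before death by day s: F(s) = a/(a+b) × [1 − exp(−(a+b)s)]. With a/(a+b) = 0.228, F(60) = 0.0325, F(120) = 0.0605 and F(180) = 0.0844.
- Rule A, restart counted only if the patient is alive and event-free at day 60. Restarted: 0.0605. Not restarted: (0.5 × 0.0844 + 0.5 × 0.0325)/(0.5 + 0.5 × 0.1427) = 0.102. Risk ratio 0.59.
- Rule B, restart counted if the patient is alive at day 60. Restarted: 0.0345 + 0.9655 × 0.0605 = 0.0929. Not restarted: (0.0844 − 0.5 × 0.8879 × 0.0929)/(0.5 + 0.5 × 0.1121) = 0.0776. Risk ratio 1.20.

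The same null truth gives apparent protection under one rule and apparent harm under the other. A simulation of 18 null scenarios agrees. It used event risk of 5–20%, mortality of 30% or 45%, and 30–50% of patients due to restart between day 14 and day 90 or 180. Never-versus-restarted odds ratios ran from 1.37 to 2.66 under rule A and from 0.68 to 0.89 under rule B. Off-versus-on rate ratios by person-time stayed between 0.97 and 1.02.

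**The case against.** The strongest reply is that the third aim is descriptive. Study design and most other mentions speak of the risk of ischaemic disease in LOAPT patients or after discontinuation, which a single cohort followed for 6 months can estimate. Presenting it by history is sensible. The resumption question is expressly left to later work, and a condensed article may leave modelling detail to an analysis plan. All of this stands. It does not cover the clause in Results that assigns the history split to the effect of discontinuing, or the association promised in the Discussion. Those assign a purpose to an analysis that cannot serve it, which is different from omitting detail.

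Three stronger readings are tempting, and the article does not support them.

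- A reader might infer that every one of the 220 LOAPT patients is a discontinuer by definition. That rests on a literal reading of an awkward sentence in Study definition that may be garbled, and the Background says that many such patients stop, not all.
- A reader might infer that the plan commits an immortal-time error by comparing patients who ever restarted with those who never did. No such comparison is stated.
- A reader might infer that restarting would be made to look protective, and more so with early deaths. The direction depends on an unstated classification rule. Early deaths shorten the time at risk of those who never restart, which weakens or reverses the bias: under rule A with 10% event risk, restart at day 30 or 60 and deaths concentrated early (assumed), risk ratios run from about 0.7 to 1.1.

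**Conclusion.** The concern holds in a limited form. The article attributes to a history subgroup analysis a conclusion about discontinuation that it cannot deliver, and no other comparison described supplies it. This is so whichever way the LOAPT definition is read, because even if some patients continued treatment the plan does not compare them with those who stopped.

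The reach is one exploratory aim. The descriptive objective can be answered, and the mortality and postoperative bleeding comparisons are untouched. The size of any misleading result cannot be stated, since the article gives no ischaemic event rate, no restart frequency and no restart times. The ratios in the working illustrate direction under assumptions and are not estimates for this study. The 84 expected deaths rest on the article's own unpublished 2019 rates at its planned group sizes.

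**What to change.** - Restate the aim as the cumulative incidence of ischaemic events to 6 months in LOAPT patients, with death as a competing event, described by prior-history subgroup.
- Remove the claim about the effect of discontinuing from that subgroup analysis, and align the Discussion's promise of an association with it.
- Clarify the sentence in Study definition so that it is plain whether discontinuation is a condition of being on LOAPT.
- If any on-versus-off treatment claim is to be made, record stop and restart dates within the medication data already collected. Analyse antiplatelet status as a time-dependent exposure in a cause-specific Cox model, with adjustment for prognostic factors including history. This removes the classification problem but not confounding by the reasons for restarting, so the result should be reported as an association.

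The cost is a change of wording, the dates if they are not already captured, and a more modest claim. Recruitment and the two main comparisons do not change.
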